### Culture proven late onset sepsis

Defined as sepsis diagnosed >72 h of age, confirmed with a positive blood and/cerebral spinal fluid specimen.

### Days to reach full enteral feeding

The number of days required to reach 150 ml/kg/day of enteral nutrition, counted from day when milk is started.

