#### Control group

Patients will receive enteral feeding at the discretion of the leading physician. Feeding practice differs between staff and usually relies on an increase of enteral feeding by 5–20ml/kg/day. Subjective evaluation of feeding tolerance, will be defined as one of the following: bilious or milk residuals, distended abdomen, and vomiting. Withholding or slowing down feeding will be subject to an induvial decision of the attending.

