#### Study group

To meet the nutritional goals, infants will receive enteral feeding based on the following protocol (14):

Minimal enteral nutrition (MEN) will begin within 72 h life at 10 to 20 mL/kg/day, breast milk/donor human milk. MEN will not be included in the caloric goals.Advancements in feeding will be set at 20–30 mL/kg/day, but not more than 10 ml per feeding portion to reach a goal of 150 ml/kg/day, but not more than 120ml/kg/day in cases of fluid restriction).The goal will be to reach an overall daily caloric intake of minimum 100 kcal/kg/d.

In both groups the interventions will continue up to 28 days of life or day of cardiosurgical treatment, whichever comes first.

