### Statistical methods

#### Statistical methods for primary and secondary outcomes

As the trial is designed as a superiority study, both primary and secondary outcomes will be analyzed based on the per-protocol (PP) approach.

For primary outcomes and dichotomous secondary outcomes, between-group differences, and the two-sided 95% confidence interval (CI) for the estimated difference approach will be used (47–49).

For continuous outcomes, means/medians and 95% CIs will be calculated. Differences in changes from baseline between treatment groups will be compared using a two-sample t test or Mann-Whitney *U*-test (50).

Additionally, a predictive model to clarify the risk of NEC complications in both study groups will be implemented. Statistical and machine learning techniques such as decision trees, random forests, and support vector machine (SVM) will be used (51–55).

All statistical calculation will be carried out using R package (The R Foundation Vienna, Austria) and Statsoft (Hamburg, Germany).

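### Days to full enteral feeding is fixed at a volume that fluid-restricted study infants cannot attain while restricted, and it is counted from first milk, so differences in initiation are left out

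*Protocol article*

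**What the plan says.** The section Days to reach full enteral feeding gives the definition: "The number of days required to reach 150 ml/kg/day of enteral nutrition, counted from day when milk is started". It states no variant for fluid restriction.

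The Study group section sets the start ("Minimal enteral nutrition (MEN) will begin within 72 h life at 10 to 20 mL/kg/day"), the pace ("Advancements in feeding will be set at 20–30 mL/kg/day") and the target ("to reach a goal of 150 ml/kg/day, but not more than 120ml/kg/day in cases of fluid restriction"). It adds that in both groups "the interventions will continue up to 28 days of life or day of cardiosurgical treatment, whichever comes first".

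In the Control group section, feeding is left to the physician. Practice there "usually relies on an increase of enteral feeding by 5–20ml/kg/day". No start day and no upper volume are written.

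The Objectives section puts both starting and advancing feeds under test. The Abstract names this outcome among the secondary outcomes.

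Under Statistical methods, primary and secondary outcomes are analysed per protocol. Continuous outcomes get means or medians with 95% confidence intervals, and differences in change from baseline "will be compared using a two-sample t test or Mann-Whitney" *U*-test. The Interim analyses section allows imputation of missing data, for example multiple imputation.

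**The concern.** Three features of the outcome do not fit the trial around it.

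- **Threshold.** It is a single volume, while the study regimen sets a lower ceiling for some infants. For them, full compliance and attaining the outcome exclude each other as long as the restriction lasts.
- **Time origin.** For an infant not yet fed at randomisation, first milk comes after allocation. The study arm has a deadline for it and the control arm does not. A clock that starts there removes any difference in time to initiation.
- **Infants without a value.** Restriction, surgery or death can prevent attainment. The tests named for continuous outcomes need a number for every infant.

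At stake is the interpretation of the outcome that most directly measures progress to full feeds. A study-arm gain from earlier starting would not appear in it. The comparison of days could also rest on subsets of the two arms that differ in ways related to treatment.

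**Working it through.** The plan gives no figure for this outcome, so there is none to reproduce. The check uses days = (target − start) / daily step, with the ranges in the Study group and Control group sections. It ignores pauses and the separate limit per feeding portion.

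**1. Threshold against ceiling.** 150 − 120 = 30 ml/kg/day, and 30/150 = 20%. An infant held at 120 does not qualify however long it is fed at that volume.

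**2. Study arm, unrestricted.** Fastest: (150 − 20)/30 = 4.3 days. Slowest: (150 − 10)/20 = 7 days. A restricted infant reaches its ceiling of 120 in (120 − 20)/30 = 3.3 to (120 − 10)/20 = 5.5 days. It has met its regimen's target and has no value for the outcome.

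**3. Control arm.** No starting volume is given; 5–20 ml/kg/day is assumed.

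| Daily step (ml/kg/day) | From 20 | From 5 |
|---|---|---|
| 20 | 130/20 = 6.5 days | 145/20 = 7.25 days |
| 10 | 130/10 = 13 days | 145/10 = 14.5 days |
| 5 | 130/5 = 26 days | 145/5 = 29 days |

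At the slowest usual pace, attainment falls near or after day 28 of life, when the allocated feeding ends. Surgery can come sooner in either arm.

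**4. Time origin.** Infant A starts milk on day 8 and reaches 150 on day 16: 16 − 8 = 8 days. Infant B starts on day 2 and reaches it on day 10: 10 − 2 = 8 days. If both were randomised on day 2 (assumed), the times from randomisation are 16 − 2 = 14 and 10 − 2 = 8 days. The 6-day difference in attainment is invisible in the outcome as defined.

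**5. What a comparison of attainers only would do (illustration; the plan does not specify it).** Assumptions:
- daily steps uniform on 20–30 (study) and 5–20 (control) ml/kg/day;
- starting volumes uniform on 10–20 and 5–20 ml/kg/day;
- first milk on days 1–3 and 1–5;
- observation ends at day 28, or at surgery on day 4 plus an exponential time with mean 8 or 14 days, or with no surgery;
- 0–40% of infants restricted throughout, the same share in both arms.

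If every infant could be followed to 150, the control-minus-study difference is about 7.3 days. Among attainers only it is 4.8 to 6.8 days. The shrinkage comes from early end of observation, which removes slow feeders. Restriction, assigned here independently of pace, leaves the difference almost unchanged (4.78 days at 0% and 4.80 at 40%, surgery mean 8) but lowers the study-arm share with a value from 62% to 37%.

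**The case against.** **The statistical analysis plan is not shown.** Handling of infants who never reach the volume may be written there, and silence in an article is no fault. That is right, and it limits the third feature. It does not touch the first two, which are in the printed definition.

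**A reader might infer that such infants are dropped.** The text does not say so. It provides imputation for missing data and keeps infants who stop the intervention on study. Imputation is still a poor answer here: for an infant who is capped or who dies first, the value does not exist rather than being unobserved.

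**A reader might infer that the slowest controls can never contribute.** That does not follow. Day 28 limits the intervention, not this outcome. A 30-day figure (150/5) assumes a start from zero, against 26 to 29 days in the table above, and a step of 5 is only the low end of usual practice.

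**Restriction need not be permanent.** An infant whose restriction is lifted can still reach 150, and discretionary control feeding may be restricted too. Both points stand. The conflict therefore concerns infants while restricted, and how unevenly it falls on the arms is unknown.

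**The test sentence is about change from baseline,** which a number of days does not have, so applying it to this outcome is an inference. It is nevertheless the only between-group test named for continuous outcomes. A Mann-Whitney test could rank non-attainers last, but that rule is not stated, and it would treat an infant sent early to surgery as a slow feeder.

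**Time from first milk is a coherent measure of advancement speed,** and earlier starting may show in the daily intake outcomes. Also true, but the objective covers initiation, and the Eligibility criteria section itself describes full feeding by day of life, a different origin.

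**Conclusion.** The point holds in a limited form. The definition conflicts with the Study group section for fluid-restricted infants, and its time origin leaves out initiation. Infants who stay restricted, or who have surgery or die before attainment, have no meaningful number of days, and the named tests do not handle that.

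The consequence is a risk of bias, not a demonstrated bias. Its size and direction depend on the share restricted in each arm, the timing of surgery, and when controls start milk, none of which is given. It would go too far to conclude that the result will point the wrong way or that the infants lost are mainly controls: the ceiling is written for the study arm, slow advancement is more likely in the control arm, and in the illustration the difference shrinks but keeps its direction. The illustration rests on assumed distributions and shows only that selection on attainment can matter.

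This is one secondary outcome. The NEC comparison and the sample size do not depend on it.

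**What to change.** 1. Reconcile the Study group section with the outcome definition, so that attainment has one objective definition applied identically in both arms. The clinical team should settle the volumes. A target set by each infant's prescriber would not serve: prescribers are unblinded, and the threshold could then differ by arm.
2. Count from randomisation.
3. Analyse all randomised infants as time to event: cumulative incidence over a fixed, stated window, with surgery and death before attainment as competing events, compared by Gray's test stratified by lesion type (the randomisation factor).
4. Keep time from first milk as a descriptive measure of advancement speed.

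The cost is a change of wording in the outcome definition and the analysis plan. The analysis needs daily enteral volume and the dates of randomisation, surgery and death; the date of first milk serves the descriptive measure. The article lists daily energy and protein intake but not volume, so confirm that volume is captured. The downside is that the result is a cumulative incidence or median time rather than a mean number of days.

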### Days on mechanical ventilation

The number of days on mechanical ventilation.

### Breastfeeding

Breastfeeding assessment at 3, 6, and 12 months of age. Exclusive breastfeeding will be defined as feeding infants only breast milk, directly from breast or expressed, except drops or syrups consisting of vitamins, mineral supplements, or medicine (29). Partial breastfeeding will be defined as the infant receiving human and formula milk (30).

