**Assessments**								
feeding tolerance	x	x	x	x	x			
ECHO assessment	x	x	x	x	x			
Mesenteric and renal artery assessment	x	x	x	x	x			
Anthropometrics weight length head circumference						x	x	x
Breast feeding assessment						x	x	x

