### Participant timeline

T0- day 1 of lifeT1- day 3 of lifeT2- day 7 of lifeT3-day 14 of lifeT4-day 28 of lifeT5- 3 months of ageT6 - 6 months of ageT7- 12 months of age.

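### At 12 months, and partly at 6, the two breastfeeding categories leave out infants on human milk and complementary food without formula, so continued breastfeeding cannot be measured

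*Protocol article*

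**What the plan says.** Under the secondary outcomes, the Breastfeeding section of the Protocol article sets the schedule: "Breastfeeding assessment at 3, 6, and 12 months of age". It then defines two terms. The first is "Exclusive breastfeeding will be defined as feeding infants only breast milk, directly from breast or expressed, except drops or syrups consisting of vitamins, mineral supplements," with medicine as the last exception. The second is "Partial breastfeeding will be defined as the infant receiving human and formula milk".

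The Participant timeline agrees with the schedule: T5 to T7 are "3 months of ageT6 - 6 months of ageT7- 12 months of age". Table 1 (Study timetable) has a row "Breast feeding assessment" marked at those three visits.

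Neither definition is limited to an age. The document does not mention complementary food or solids, and it names no third category.

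**The concern.** Both definitions work while milk is the whole diet. They are nevertheless applied unchanged up to 12 months, when milk is ordinarily only part of it. From the start of solids no infant can be *exclusive*, and *partial* is open only to infants who also take formula. A child still breastfed at 12 months, eating family food and never given formula, has no place in the scheme.

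That pattern is plausible in this trial. The Exclusion criteria remove infants whose enteral feeding is more than half formula. The Study group section specifies breast or donor milk. Study setting provides a daily breastfeeding consultant, and Recruitment offers mothers extra breastfeeding support. Families of this kind are likely to include some who continue human milk without formula.

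At stake is whether the 12-month result, and part of the 6-month result, says anything about continued breastfeeding. The Statistical methods section compares dichotomous secondary outcomes as between-group differences with 95% confidence intervals, which requires a clear yes or no for each infant.

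**Working it through.** No sample size, power or event count is involved, and the plan gives no figure to reproduce. The check is logical: apply the two definitions literally to every combination of human milk (H), formula (F) and complementary food (S).

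| Diet | Exclusive? | Partial? | Result |
|---|---|---|---|
| H | yes | no | exclusive |
| H + F | no | yes | partial |
| H + F + S | no | yes | partial |
| H + S | no (more than breast milk) | no (no formula) | **no category** |
| F, S, F + S, or none of the three | no | no | no human milk; no category is named |

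Three things follow.

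1. Of the four diets that contain human milk, exactly one, H + S, has no category. H + F + S still counts as *partial*, because that definition asks for both milks and does not rule out food.
2. Both rows that combine human milk with solids fail *exclusive*. Among infants who have started solids that category is empty in each arm, whichever milk they receive, and a comparison of two empty categories carries no information.
3. Among those same infants, the only way to be recorded as breastfed is to take formula as well. The rate of *partial* then depends jointly on continued human milk and on formula use, and the two cannot be separated.

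Could *exclusive* be read as referring to milk source only, so that solids do not count against it? The wording is against this. It says "Exclusive breastfeeding will be defined as feeding infants only breast milk, directly from breast or expressed" and then lists what is excepted. Because vitamins, minerals and medicines needed an exception, the definition covers everything the infant swallows, and food is not among the exceptions.

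By visit:
- **3 months:** the categories work, provided no solids are given.
- **6 months:** the gap applies to infants who have started solids. The document does not give this share.
- **12 months:** nearly all infants are affected, assuming ordinary infant-feeding practice.

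The number of infants in the H + S row cannot be computed. It would need the share still on human milk and the share of those taking no formula, and the document gives neither.

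**The case against.** The strongest reply has four parts.

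**The article states no harmful coding rule.** A reader might infer that unclassified infants are counted as not breastfed, so that families avoiding formula score below families using it and the ranking is reversed. The Breastfeeding section does not say so. It names no not-breastfed category, does not call its two terms exhaustive and sets no order between them. This part stands: the defect is an unclassified diet, not a reversed scale. A comparison pointing the wrong way would also require the arms to differ in formula use after discharge. Nothing in the document indicates that they will, and the intervention ends at 28 days or at cardiac surgery, whichever is first.

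**Wrong rates and a size are not shown.** A reader might conclude that two of the three assessments give wrong rates. A rate of *exclusive* near zero at 12 months would be correct under its definition, only uninformative, and the effect at 6 months is unknown. One could assume that 20–40% of infants still receive human milk at 12 months and that half of these take no formula, which gives 0.20 × 0.5 = 0.10 to 0.40 × 0.5 = 0.20 of all infants. Both inputs are assumptions, and calling those infants misclassified needs the unstated coding rule. The figure should not be used.

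**The detail may sit elsewhere.** An article condenses a full protocol, and the follow-up form may record more than two labels. That is possible, but the article itself fixes both definitions and applies them at all three ages. This is a stated rule that fails at a stated time, not a detail left out. If the form recorded only the two labels, no later analysis plan could recover whether solids or formula were given.

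**It is a small outcome.** Breastfeeding is one of many secondary outcomes, is not named in the Abstract or the Objectives, and plays no part in the sample size or interim stopping. This stands and limits the weight of the point.

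**Conclusion.** The point holds in a limited form. Read literally, the definitions give no category to an infant on human milk and complementary food without formula. At 12 months *exclusive* is essentially empty in both arms and the remaining breastfed category requires formula, so the comparison cannot measure continued breastfeeding. At 6 months the same is true for those who have started solids. The 3-month assessment is sound if no solids are given.

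This rests on the wording of the Breastfeeding section and on one outside assumption, that nearly all infants eat complementary food by 12 months. The number of infants affected cannot be derived.

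It would also be too broad to say that the categories fail for every infant on solids, since human milk with formula and solids still fits *partial*. The consequence is limited to this secondary outcome. It is worth correcting because the correction costs almost nothing and is best made before the follow-up data are collected.

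**What to change.** 1. Redefine *partial* as human milk plus any other milk or food. This alone closes the gap in the categories.
2. Report any human milk (yes/no, whatever else the infant eats) at 6 and 12 months.
3. Record formula and complementary food as separate items at each follow-up visit.
4. Interpret *exclusive* only at ages before complementary food is introduced.

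Item 1 is the minimum. Items 2 to 4 make the 6- and 12-month comparisons interpretable, and a reported yes/no suits the planned difference in proportions. The cost is one reworded definition and one added question at visits already scheduled, with an amendment if the sponsor's procedure requires it. The primary outcome, sample size and visit schedule do not change.

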### Cardiac parameters

Anatomic lesions that disrupt systemic blood flow such as duct dependent lesion, may lead to impaired blood flow which increases the risk of NEC. Carlo et al. demonstrated that, this “diastolic steal phenomenon” appeared in 47% of infants with duct dependent CHD, who developed NEC (31).

However, there are no studies evaluating the mesenteric, aortic, and renal artery blood flow changes after the introduction of feeds.

Doppler assessment will be performed on 1, 3, 7, 14, 28 day of life.

The following measurements will be recorded.

Peak systolic velocity (PSV) in (cm/s).End-diastolic velocity (EDV) in (cm/s).Resistivity index (RI).Pulsation index (PI).Superior mesenteric artery (SMA) blood flow assessment will be performed using the sagittal plane of the abdominal cavity, in the longitudinal projection of the vessel, 1 cm below the celiac trunk.Right renal artery (RRA) blood flow assessment will be performed using the frontal plane of the abdominal cavity when the hilum of the kidney is visualized (32).direction of diastolic flow in the post-ductal aorta (using pulsed Doppler) will be defined as antegrade, absent or retrograde flow (32).

### Age at transfer

The age (in days) at transfer to a cardiac referral center will recorded, including the length of hospital stay in the referring center, and the reason for transfer.

### Participant timeline

T0- day 1 of lifeT1- day 3 of lifeT2- day 7 of lifeT3-day 14 of lifeT4-day 28 of lifeT5- 3 months of ageT6 - 6 months of ageT7- 12 months of age.

### Sample size

Studies have reported an incidence of NEC between 7–20% in babies with duct dependent congenital heart diseases, hence we chose the incidence of 18% in the control arm and 7.6% the intervention group (7, 14, 33–35). Therefore, 192 neonates should be included in each group. In total (assuming 20% lost for follow up), 384 neonates with a duct dependent heart disease should be included in the study. These calculations were performed assuming superiority *H0: P1* = *P2* vs. *H1: P1*≥*P2* with a power of 80%, a significance level of 5%. References: https://select-statistics.co.uk/calculators/sample-size-calculator-two-proprtions/ (36).

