#### Eligibility criteria

All parents of infants diagnosed with a duct dependant lesion and admitted to participating units will be approached by one of the research team members within the first 72 h of life (as full enteral feeding is usually reached at a minimum of 7 days of life). He or she will explain the study and obtain written consent for participating in the trail. Recruitment will take place between June 1st 2022 and June 30st 2024. After obtaining written consent for participating in the trial, the patient's medical record number (MRN) will be immediately registered on REDCap (Research Electronic Data Capture). Patients eligible for the trial must comply with all the following **at randomization**.

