### Recruitment

The study will continue until the minimum of 192 valid observations are collected in every arm. As part of the antenatal cardiology consult, women with will be offered a short meeting with a member of the recruitment team. During this appointment, they will be offered participation in the trial. To increase participant enrolment a second patient screen will be carried out by medical staff during admission to the Neonatal Intensive Care Unit. The enrolment period will extend over 36 months. Recruitment rates will be monitored monthly. In return, women will be offered additional breastfeeding support.

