#### Plans to promote participant retention and complete follow-up

All randomized infants who are prematurely discontinued from study drug will be considered *off study intervention/on study*. They will follow the same participant timetable as those infants who continue study intervention. All these infants will be followed through 12 months as scheduled.

Once an infant is enrolled or randomized, the study site will make every reasonable effort to follow the infant for the entire study period. It is projected that the rate of loss-to-follow-up on an annual basis will be at most 20%. Each study site staff will develop and implement local standard operating procedures to achieve this level of follow-up.

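### The sample size section gives 192 per arm as the number to enrol with 20% loss assumed, while the recruitment section requires 192 valid observations per arm; at that loss both cannot hold

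*Protocol article*

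**What the plan says.** All references are to the protocol article.

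- **Sample size.** The design rates are given as "we chose the incidence of 18% in the control arm and 7.6% the intervention group", "with a power of 80%, a significance level of 5" per cent. The conclusion is "192 neonates should be included in each group. In total (assuming 20% lost for follow up), 384 neonates". The hypotheses are written as H0: P1 = P2 against H1: P1 ≥ P2, which is directional.
- **Recruitment.** "The study will continue until the minimum of 192 valid observations are collected in every arm". The same section says "The enrolment period will extend over 36 months".
- **Eligibility criteria.** "Recruitment will take place between June 1st 2022 and June 30st 2024".
- **Plans to promote participant retention and complete follow-up.** "It is projected that the rate of loss-to-follow-up on an annual basis will be at most 20" per cent, with infants followed to 12 months.
- **Study group.** In both arms the intervention ends at 28 days of life or at cardiac surgery, whichever is earlier.
- **Statistical methods for primary and secondary outcomes.** For the primary outcomes "the two-sided 95% confidence interval (CI) for the estimated difference approach will be used". The primary analysis is per protocol.

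**The concern.** The figure 192 has two incompatible meanings. In the sample size section it is a count of infants to include, before loss. In the recruitment section it is a count of valid observations, after loss. The total of 384 is exactly 2 × 192, so nothing is added for loss between the per-arm figure and the total. If 192 is the pre-loss number, the recruitment rule asks for more than 384 can supply at 20% loss. If 192 is the post-loss number, 384 contains no loss allowance although the text says that it does.

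This matters because the recruitment sentence decides when randomisation of neonates stops. As written, the trial could end at 384 randomised or run to 480, over either of two recruitment periods, with a power that differs from the stated 80% in either case.

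**Working it through.** **Inputs.** p1 = 0.18, p2 = 0.076, power 80% and alpha 5% (Sample size); two-sided, from the planned confidence interval (Statistical methods); 1:1 allocation (Trial design); 20% loss (Sample size). Then p1 − p2 = 0.104, mean p = 0.128, p1(1 − p1) + p2(1 − p2) = 0.1476 + 0.0702 = 0.2178, z(0.975) = 1.960 and z(0.80) = 0.842.

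**1. Evaluable number per arm**

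- Unpooled: n = (1.960 + 0.842)² × 0.2178 / 0.104² = 158.1, so 159.
- Pooled: n = [1.960 × √(2 × 0.128 × 0.872) + 0.842 × √0.2178]² / 0.104² = 160.8, so 161.

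**2. Reproducing 192**

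- 160 × 1.2 = 192 exactly. From 159 and 161 the same step gives 191 and 194.
- Dividing by 1 − 0.2 instead gives 160/0.8 = 200, or 199 and 202 from 159 and 161 (398 to 404 in total).
- An arcsine formula gives 156, and 156/0.8 = 195, which is close to 192 but not equal.
- A two-sided continuity-corrected formula gives 180 with no loss allowance, and 216 (× 1.2) or 225 (/0.8) with one.
- One-sided 5%, as the stated H1 suggests, needs only 125 (unpooled) to 127 (pooled). With a 20% allowance that becomes 150 to 159. It does not lead to 192.

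The likeliest route is therefore a two-sided calculation with 20% added to 160.

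**3. What each section implies at 20% loss**

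- 384 randomised: 192 × 0.8 = 153.6 analysable per arm.
- 192 valid per arm: 192/0.8 = 240 randomised per arm, 480 in total, which is 480 − 384 = 96 more infants.

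**4. Power**

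Pooled power = Φ{[0.104 × √n − 1.960 × √(2 × 0.128 × 0.872)] / √0.2178}.

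| Analysable per arm | How it arises | Power, pooled | Power, unpooled |
|---|---|---|---|
| 154 | 384 randomised, 20% lost | 78% | 79% |
| 192 | recruitment rule met, or 384 randomised with no loss | 86.5% | 87% |

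With 384 randomised, pooled power is 82.8% at 10% loss (172.8 per arm) and 80.1% at 16% loss (161.3 per arm). The break-even loss is 1 − 160.8/192 = 16%.

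**5. Recruitment period**

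1 June 2022 to 30 June 2024 is 25 months; the recruitment section says 36. For 384 infants this means 384/25 = 15.4 or 384/36 = 10.7 per month.

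**The case against.** The strongest reply is that the conflict depends on 20% of primary outcomes really being lost. The retention section calls 20% an annual maximum, and follow-up runs to 12 months. The intervention ends by day 28 or surgery. If NEC is counted over that period, few infants may be lost to the primary outcome. With nearly complete data, 384 randomised, about 192 valid per arm and at least 80% power are compatible. This stands, and it limits the size of the problem. It does not remove it, because the sample size section applies 20% to this very calculation. In addition, the primary analysis is per protocol, so analysable numbers depend on adherence as well as on known NEC status.

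A reader might go further in four ways that the documents do not support.

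- **That 80% power is reached under neither reading.** With 192 valid per arm, power is about 87%, which exceeds the target. With 384 randomised it stays at or above 80% up to about 16% loss.
- **That the loss allowance is proven to be miscalculated.** The protocol does not show the uninflated number. The × 1.2 step is well supported but inferred, and the arcsine route comes near 192 by correct division.
- **That the interim schedule settles the matter in favour of 384.** Three looks at every 100 recruits fit 384 better than 480. However, the protocol lets the chair of the data monitoring committee, in consultation with the steering committee, change the schedule, and it allows sample size re-estimation.
- **That adopting 384 randomised is a change of wording only.** The recruitment section sets a floor of 192 valid observations, and replacing it gives up the power which that floor secures.

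**Conclusion.** The concern holds in a limited form. At the protocol's own 20% loss, the total of 384 and the rule of 192 valid per arm contradict each other by 96 infants. The likely inflation slip is small: about 7 to 10 infants per arm (199 to 202 instead of 192) and 1 to 2 points of power, leaving 78–79% against the stated 80% if the full 20% are lost. If 192 per arm are valid, power is about 87%. These figures assume rates of 18% and 7.6%, a two-sided 5% test and normal approximations.

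Two further inconsistencies need no assumption about loss. The directional H1 disagrees with the two-sided interval and does not reproduce 192. The recruitment periods of 25 and 36 months contradict each other. The passages need to be reconciled, but the trial is not shown to be seriously underpowered on its design rates.

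**What to change.** 1. **Sample size.** State that about 161 evaluable infants per arm give 80% power at two-sided 5%. Add that 384 randomised give about 78% power if 20% are not analysable and about 87% if all are analysed. Write H1 as P1 ≠ P2.
2. **Recruitment.** Say whether the target counts randomised or analysable infants, and make it agree with the sample size section. One option is to end recruitment at 384 randomised.
3. **Eligibility criteria and Recruitment.** Use one recruitment period.

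**Cost.** The H1 and date changes are wording. Keeping 384 lowers the stated power by 1 to 2 points at 20% loss. Measured against the current floor of 192 valid per arm, it gives up an assured 87% or so and could end at 78–79%, a loss of up to 8 to 9 points. Keeping the floor instead means up to 96 more infants at 20% loss. Keeping 80% power at the full 20% loss by division would need about 400 to 404 randomised (2 × 200 to 2 × 202), which is 16 to 20 more than 384. The authors should choose which number governs; the text does not decide it.
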